### Recruitment

Patients will be recruited from urology departments of participating hospitals. Eligibility will be assessed based on cystoscopic findings suspicious for MIBC, in the absence of lymph node or distant metastases with imaging. The participating urologists will inform eligible patients about the study and obtain written informed consent. A model of the Dutch informed consent form is provided in online supplemental file 1. We anticipate that the collaboration with 15 hospitals, including academic and large teaching hospitals, will provide a sufficient number of eligible patients to reach the required sample size.

### Randomisation: sequence generation, allocation concealment mechanism and implementation

Patients will be randomised in a 1:1 ratio to either the standard TURBT arm or the intervention arm (mpMRI with same-day biopsy). Randomisation will be performed using a computer-generated allocation sequence, stratified by study centre and by cystoscopy Likert score 4–5 vs <4. A central web-based randomisation system will be used to ensure allocation concealment. The allocation sequence will be generated by an independent data manager not involved in patient enrolment or treatment assignment.

Treating physicians and study staff responsible for patient enrolment will not have access to the allocation sequence. After eligibility is confirmed and informed consent is obtained, the treating urologist or study coordinator will log into the secure system to randomise the patient. The allocated arm will then be revealed to the study team for further planning of diagnostic procedures and treatment.

### Blinding

Given the nature of the interventions, blinding of participants and treating physicians is not feasible. However, the central review of mpMRI scans is performed by blinded radiologists, who will be unaware of clinical information, pathology, and the other readers' scores. Similarly, central pathology review will be performed blinded to the assigned intervention. Data analysts will also be blinded to treatment allocation during statistical analysis. There are no procedures for unblinding, as treatment allocation is not concealed during clinical care.

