**Methods and analysis:**

BladParadigm is a two-arm multicentre randomised controlled trial (RCT) conducted in the Netherlands. Over a 3-year period, patients with clinically suspected MIBC without evidence of metastases will be recruited and randomised 1:1 to either TURBT or 3-Tesla mpMRI with same-day outpatient bladder biopsy. The Vesical Imaging Reporting and Data System (VI-RADS) will be used to standardise mpMRI reporting. Patients will undergo definitive treatment based on the results of the TURBT or mpMRI. The study is powered to demonstrate that the mpMRI-based strategy is at least non-inferior to standard TURBT in patients treated with radical cystectomy alone, assuming a relative hazard of 0.55. The required sample size is 360 patients (180 TURBT, 180 mpMRI). The primary outcome is 2-year progression-free survival. Progression will be assessed by imaging, according to the current standard of care. Secondary outcome measures are time to definitive treatment, quality of life (EuroQol 5D-5L), healthcare costs and cost-effectiveness.

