**Trial registration number:**

NCT05779631.

STRENGTHS AND LIMITATIONS OF THIS STUDYThis is one of the first, large, multicentre, randomised controlled trials comparing a multiparametric MRI (mpMRI)-based diagnostic pathway to current standard of care, both in academic and community hospitals.All mpMRI scans follow a standardised Vesical Imaging-Reporting and Data System–based protocol for acquisition and reporting.All mpMRI scans will be double-read to ensure robust diagnosis.At the end of the study, transurethral resection of the bladder tumour and radical cystectomy specimens of the intervention arm will undergo central review to assess the diagnostic validity of mpMRI.Inclusion is based on cystoscopic assessment, which is subjective and may vary between clinicians.

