##### Treatment and follow-up

Results from the mpMRI and biopsy are discussed in a multidisciplinary tumour board, where definitive treatment plans will be determined. Patients with a VI-RADS score of 1 or 2 will be classified as having NMIBC and will typically undergo TURBT, often supplemented by bladder instillations and/or re-TURBT. Those with a VI-RADS score of 3, 4 or 5 will be classified as having MIBC and will undergo definitive treatment, usually involving RC with or without NAC or chemoradiotherapy.

After treatment, all patients, including those in the standard care arm, will be monitored and progression will be assessed by imaging: (PET-)CT every 6 months until the third year, followed by an annual CT scan thereafter. The minimum follow-up duration for all participants in the study is 2 years from the point of randomisation. It is anticipated that patients enrolled earlier in the study can be monitored for a longer duration, potentially to 4.5 years, compared with those who enrol later.

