##### Pathology review

All resected specimens from TURBT and cystectomy will be evaluated and reported by a urogenital pathologist, following standard protocols. At the end of the study, all specimens from the intervention arm—those obtained from TURBT (when mpMRI suggests NMIBC) and RC (without NAC, when mpMRI suggests MIBC)—will undergo central review to assess the diagnostic validity of mpMRI.

It is anticipated that mpMRI will classify a maximum of 10% of patients as NMIBC, who will then undergo TURBT. The remaining 90% of patients will be classified as MIBC, with approximately two-thirds of them treated with RC alone. As a result, a central pathology review will be conducted for approximately n=120 cases. As the central pathology review is performed at the end of the trial, results do not affect the choice of definitive treatment.

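### The blind stated for central pathology review is to trial arm, but only one arm is reviewed; the blind that matters there is to the mpMRI result

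*Protocol article*

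**What the plan says.** The Blinding section deals with two central reviews. For the radiologists it lists what is hidden: clinical information, pathology and the other readers' scores. For the pathologists it gives one item only: "central pathology review will be performed blinded to the assigned intervention".

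The Pathology review section defines the set to be reviewed. It is "all specimens from the intervention arm", specified as "those obtained from TURBT (when mpMRI suggests NMIBC) and RC (without NAC, when mpMRI suggests MIBC". The expected number is about 120, and the review takes place at the end of the trial, so it cannot influence treatment. The strengths and limitations box agrees on the set and its purpose: "radical cystectomy specimens of the intervention arm will undergo central review to assess the diagnostic validity of mpMRI".

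The Treatment and follow-up section links the mpMRI result to treatment. "Patients with a VI-RADS score of 1 or 2 will be classified as having NMIBC and will typically undergo TURBT". "Those with a VI-RADS score of 3, 4 or 5 will be classified as having MIBC and will undergo definitive treatment", which it describes as usually cystectomy, with or without neoadjuvant chemotherapy, or chemoradiotherapy.

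**The concern.** If every reviewed specimen comes from the same arm, blinding to arm protects against nothing. The review has one stated purpose, to assess mpMRI, and so serves as the reference standard against which VI-RADS is judged. Such a reading needs protection from knowledge of the index test and of the local stage. The Blinding section fixes a blind for this review, but on another item.

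At stake is the credibility of the trial's own accuracy figures for mpMRI. The Discussion defends counting VI-RADS 3 as muscle-invasive with accuracy figures from other studies and with an estimate that overtreatment is likely below 5%. The central review is where the trial can check those figures on its own patients. A pathologist who knows the mpMRI result could be influenced by it when muscle invasion is hard to call, and a report repeating the present sentence would describe a safeguard with no content.

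**Working it through.** **1. Does the stated number fit a one-arm review?** Inputs: 180 patients in the intervention arm (Abstract: "The required sample size is 360 patients (180 TURBT, 180 mpMRI"); a share f of at most 10% classed as NMIBC by mpMRI, who have TURBT; and about two-thirds of the remainder treated with cystectomy alone (both from Pathology review). The Sample size section gives about 65% for cystectomy alone, so both values of r are tried.

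Reviewed cases = 180 × f + 180 × (1 − f) × r

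- f = 0, r = 2/3: 0 + 120 = 120
- f = 0.10, r = 2/3: 18 + 108 = 126
- f = 0, r = 0.65: 0 + 117 = 117
- f = 0.10, r = 0.65: 18 + 105.3 = 123.3

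The stated figure of about 120 is reproduced from the intervention arm alone.

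**2. Could the standard arm be included?** Every standard-arm patient is assigned to TURBT, about 180 specimens. Adding these alone gives 120 + 180 = 300 or more, before any standard-arm cystectomies. That does not fit 120. The sentence in Pathology review covering all TURBT and cystectomy specimens concerns routine reporting by a urogenital pathologist, not the central review.

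**3. What does the stated blind conceal?** Arm takes one value across the reviewed set. A variable that does not vary cannot differentially influence readings within the set, so concealing it has no effect on the accuracy assessment.

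**4. What does specimen type reveal?** Setting Pathology review beside Treatment and follow-up:

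- TURBT specimen: mpMRI suggested NMIBC, VI-RADS 1-2 (at most 18 cases)
- Cystectomy specimen without neoadjuvant chemotherapy: mpMRI suggested MIBC, VI-RADS 3-5 (about 105 to 120 cases)

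A reader who knows this rule can infer the two-way class from the type of tissue. The score within each class is not revealed.

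**5. Can the bias be sized?** No. The documents say nothing about how often a pathologist's call would change. Nor can the reviewed set be reconstructed from the Discussion's accuracy figures. With sensitivity 92%, specificity 84% and prevalence 72% to 78%, the share classed VI-RADS 1-2 would be:

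- at 72%: 0.08 × 0.72 + 0.84 × 0.28 = 29.3%
- at 78%: 0.08 × 0.78 + 0.84 × 0.22 = 24.7%

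Pathology review expects at most 10%. Any bias figure built on those inputs would describe a different set from the one the article plans to review.

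**The case against.** The strongest reply is that this is a condensed article. A full protocol and SAP exist, and what a central pathologist is shown is operational detail usually kept there. The pathology sentence also follows directly on the radiologists' masking and is presented as similar to it, so comparable masking may be intended. This stands in part: the lack of a full list of masked items would not be a finding by itself. But the article is not silent. It names an item, and for a one-arm review that item is the wrong one.

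A reader might infer more, and the documents do not support it:

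- *That the stated blind is impossible.* Both arms produce TURBT and cystectomy specimens, so tissue type does not disclose arm. A pathologist reading coded slides without knowing the selection rule could be unaware of it. The article neither describes nor excludes this. The blind is purposeless, which is a weaker statement.
- *That specimen type contradicts the Blinding section.* That section does not promise blinding to the mpMRI result. Specimen type shows that the useful blind would be incomplete; it is not a second contradiction.
- *That the mpMRI class is known in every case.* Treatment is described as typical or usual, and the Discussion expects some understaged tumours to be found at the later TURBT. The link is close under the set's definition, but not guaranteed.
- *That accuracy will be inflated by a given amount.* Step 5 shows why no such figure can be derived.

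The reply that impact is small also stands. The review affects neither PFS, time to progression, any listed secondary outcome nor any treatment decision.

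**Conclusion.** The mismatch is established from the text: a blind to assigned intervention is claimed for a review that contains one assigned intervention, and the figure of about 120 confirms the one-arm set. The masking that an accuracy assessment needs, to the index test, is not the one named. Masking to the two-way mpMRI class can only be partial because of specimen type; masking to the exact score remains possible.

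All of the roughly 120 reviewed cases are covered by the misdirected blind, but the consequence is limited to the mpMRI accuracy assessment and cannot be quantified from the documents. The conclusion rests on two assumptions: that the review set is as Pathology review defines it, and that no undisclosed standard-arm slides are added. Severity: minor.

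**What to change.** In the Blinding section, replace the sentence on central pathology with one stating that central pathologists read coded slides and are masked to VI-RADS score, MRI and cystoscopy reports, and local pathology stage. Drop the claim of blinding to assigned intervention. Add as a limitation that specimen type largely reveals the VI-RADS 1-2 versus 3-5 class to a reader who knows how the set was selected.

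Mixing in a few standard-arm slides would not remove that limitation: with at most 18 intervention-arm TURBT cases, most TURBT slides would still be VI-RADS 1-2 unless many were added, and the planned number would then need revising.

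The cost is slide coding and a less favourable blinding statement. The review happens only at the end of the study, so there is time to make the change.

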### Data management

All study data related to data collection, randomisation and trial management will be handled digitally through the CASTOR electronic data capture system. Physical informed consent forms and quality of life (EQ-5D-5L) questionnaires will be collected and stored centrally in a secure location. Both the digital data in CASTOR and the physical documents will be managed and retained in accordance with applicable privacy and security regulations, with a minimum retention period of 15 years. Data management procedures include measures to ensure data quality and integrity, such as double data entry and validation checks to minimise errors. The dataset generated during the study will be made available on reasonable request in compliance with FAIR Data Principles.

### Statistical methods

PFS (and TTP) in both trial arms will be compared in an ITT analysis using Kaplan-Meier curves and a log-rank test. In addition, we will use a proportional hazards regression model with the stratification factors (study centre and cystoscopy score 4/5) as covariates. In case of different distributions of other prognostic factors between both arms, despite the randomisation, we will adjust for these factors as well. Analyses will also be stratified by NAC (yes/no) and the Likert scale score following from visual inspection of the bladder during cystoscopy (score 4–5). We will not conduct any interim analyses.

We will compare the median time to definitive treatment between the two strategies using Kaplan-Meier analysis with a log-rank test. Missing data will be handled using multiple imputation with sensitivity analyses comparing imputed and complete case results. Prespecified subgroup and sensitivity analyses, for instance, stratified by use of neoadjuvant chemotherapy, will be conducted.

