### Outcomes

#### Primary outcome

The primary outcome is progression-free survival (PFS) at 2 years after diagnosis. PFS is defined as the time between randomisation and the occurrence of distant metastases, nodal recurrence or death from any cause, whichever occurs first. Patients without evidence of progression will be censored at the last date of assessment. In addition to PFS, time to progression (TTP), defined as the time between randomisation and diagnosis of distant metastases or loco-regional nodal recurrence, will be analysed as well. For TTP, we consider death from any cause as a competing risk.

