### Sample size

The power calculation is based on an intention-to-treat (ITT) time-to-event analysis comparing PFS between the randomisation groups. The following parameters were used: alpha two-tailed=0.05, beta (1-power)=0.20 and 1:1 randomisation. Assuming a relative hazard of 0.55, 88 events are needed. With a baseline event rate of 0.23 per year in the TURBT group, a censoring rate of 0.1 per year, and an average follow-up period of 3.25 years, 117 participants are needed in each group. Despite the fact that adding NAC to RC only provides a 5–8% increase in overall survival after 5 years compared with RC alone, the presence of NAC (or chemoradiotherapy) might still alter the impact of TURBT on prognosis. Therefore, we will conduct a stratified analysis on RC alone vs other (systemic) treatment with curative intent. In the Netherlands, less than 15% of patients with cT2-4aN0M0 MIBC are treated with chemoradiation, a little over 20% with NAC and ~65% with RC alone. That means that 117/0.65=180 patients are needed in each arm. This sample size will provide us with the necessary power to analyse our primary research question in RC-alone patients effectively.

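### Time to progression is assigned Kaplan-Meier curves although the protocol treats death as a competing risk, so progression probabilities read from those curves would be too high in both arms

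*Protocol article*

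**What the plan says.** The Primary outcome section of the protocol article defines two time-to-event outcomes. PFS runs from randomisation to "the occurrence of distant metastases, nodal recurrence or death from any cause, whichever occurs first". TTP is "defined as the time between randomisation and diagnosis of distant metastases or loco-regional nodal recurrence, will be analysed as well". Death is therefore an event for PFS but not for TTP, and the section adds: "For TTP, we consider death from any cause as a competing risk".

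The Statistical methods section gives both outcomes one analysis: "PFS (and TTP) in both trial arms will be compared in an ITT analysis using Kaplan-Meier curves and a log-rank test". It continues: "In addition, we will use a proportional hazards regression model with the stratification factors (study centre and cystoscopy score 4/5) as covariates". The article names no cumulative incidence estimator and does not say how deaths enter the TTP analysis.

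**The concern.** Kaplan-Meier suits PFS, because death is one of its events. For TTP, a Kaplan-Meier curve has to censor patients who die without progression, as if they could still progress later. Its complement estimates progression in a hypothetical setting without death, and it exceeds the actual proportion who progress as soon as any such death occurs. That does not follow the protocol's own statement about death.

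The trial's rationale is that TURBT may spread tumour cells. TTP separates metastatic and nodal spread from other deaths, so it is the outcome closest to that idea. Absolute progression risks read from its curves would be too high. The difference between arms could also be distorted, by an amount that depends on mortality without progression in each arm.

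This is more than detail left to an analysis plan. The article names a method for TTP, and that method conflicts with its own definition section.

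**Working it through.** **Step 1: reproduce the protocol's figures.** The Sample size section gives "alpha two-tailed=0.05, beta (1-power)=0.20 and 1:1 randomisation", then "Assuming a relative hazard of 0.55, 88 events are needed". It adds: "With a baseline event rate of 0.23 per year in the TURBT group, a censoring rate of 0.1 per year, and an average follow-up period". That period is 3.25 years, and the section arrives at 117 per group and 180 per arm.

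- Events (Schoenfeld): 4 × (1.960 + 0.842)² / (ln 0.55)² = 87.8, so 88.
- Probability of an observed event with event hazard l, censoring hazard c = 0.1 and T = 3.25: l/(l+c) × (1 − exp(−(l+c)T)). With l = 0.23 this is 0.4585. With l = 0.55 × 0.23 = 0.1265 it is 0.2910. The mean is 0.3747.
- Patients per group: 88 / (2 × 0.3747) = 117.4, against 117 stated. Then 117 / 0.65 = 180.

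The figures reproduce, so the protocol's hazards can be used below.

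**Step 2: formulas.** With constant hazards lp (progression) and ld (death without progression):

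- One minus Kaplan-Meier, deaths censored: 1 − exp(−lp·T)
- Actual cumulative incidence: lp/(lp+ld) × (1 − exp(−(lp+ld)·T))

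**Step 3: assumptions.** The protocol does not divide the 0.23 per year. I take 0.18 + 0.05 and 0.13 + 0.10, so that death without progression is 22% (0.05/0.23) to 43% (0.10/0.23) of the PFS hazard. For mpMRI there are two cases: (a) 0.55 multiplies both hazards; (b) 0.55 multiplies progression only and the death hazard is equal in both arms.

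**Step 4: example at 2 years, 0.18 + 0.05.**

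- TURBT: 1 − exp(−0.36) = 0.3023. Incidence is 0.7826 × (1 − exp(−0.46)) = 0.2886. The excess is 1.4 points.
- mpMRI (a), hazards 0.099 and 0.0275: 1 − exp(−0.198) = 0.1796. Incidence is 0.7826 × (1 − exp(−0.253)) = 0.1749. The excess is 0.5 points.
- mpMRI (b), hazards 0.099 and 0.05: incidence is 0.6644 × (1 − exp(−0.298)) = 0.1712. The excess is 0.8 points.

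**Step 5: all results.** Each cell gives one minus Kaplan-Meier / cumulative incidence / excess, in per cent and percentage points. The excess is taken from unrounded values.

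| Split | Years | TURBT | mpMRI (a) | mpMRI (b) |
|---|---|---|---|---|
| 0.18 + 0.05 | 2 | 30.2 / 28.9 / 1.4 | 18.0 / 17.5 / 0.5 | 18.0 / 17.1 / 0.8 |
| 0.18 + 0.05 | 3.25 | 44.3 / 41.2 / 3.1 | 27.5 / 26.4 / 1.1 | 27.5 / 25.5 / 2.0 |
| 0.18 + 0.05 | 4.5 | 55.5 / 50.5 / 5.1 | 35.9 / 34.0 / 2.0 | 35.9 / 32.5 / 3.5 |
| 0.13 + 0.10 | 2 | 22.9 / 20.8 / 2.1 | 13.3 / 12.6 / 0.7 | 13.3 / 12.1 / 1.2 |
| 0.13 + 0.10 | 3.25 | 34.5 / 29.8 / 4.7 | 20.7 / 19.1 / 1.7 | 20.7 / 17.8 / 2.9 |
| 0.13 + 0.10 | 4.5 | 44.3 / 36.4 / 7.8 | 27.5 / 24.5 / 3.0 | 27.5 / 22.4 / 5.1 |

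**Step 6: a milder split.** If only 10% of the PFS hazard is death without progression, the 2-year excess falls to 0.7 points with TURBT and to 0.2 (a) or 0.4 (b) with mpMRI.

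**Step 7: difference between arms.** In case (a) the Kaplan-Meier difference at 2 years is 12.3 points against 11.4 in actual incidence (0.18 + 0.05), or 9.6 against 8.2 (0.13 + 0.10). At 4.5 years it is 19.6 against 16.5, or 16.8 against 11.9. In case (b) at 4.5 years it is 19.6 against 18.0, or 16.8 against 14.0. If death without progression were 1.5 times as frequent with mpMRI, the discrepancy would be at most 0.7 points.

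**The case against.** A reader might infer that the whole TTP comparison is invalid and that the log-rank test should give way to Gray's test. The documents do not support that. With deaths censored, the log-rank test and the proportional hazards model are valid for the cause-specific hazard of progression. For a question about tumour seeding, that hazard is a natural target, whereas Gray's test also reflects any effect on death. The planned model, fitted with deaths censored, already is the cause-specific Cox model for progression. What is missing is the label.

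A reader might also infer that the trial's main result is at risk. It is not. TTP is analysed in addition to PFS, does not appear in the list of secondary outcomes, and plays no part in the sample size.

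Other points on this side also carry weight. The sizes rest on an assumed split. The largest need 43% of PFS events to be deaths without progression and a follow-up that only the earliest recruits might reach. The text says that arms will be compared using the curves; it does not say that their complement will be reported as absolute risk. The single sentence covering both outcomes may be shorthand, and a separate analysis plan, available on request, may specify cumulative incidence. This lowers certainty about what will be done, but the conflict in the published text remains.

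**Conclusion.** The conflict is real and confined to the TTP curves. If the text is followed, one minus Kaplan-Meier is too high in both arms; the direction is certain once any patient dies without progression. At the protocol's 2-year horizon the effect is modest on the assumed splits: 1.4 to 2.1 points with TURBT, and 0.5 to 0.7 or 0.8 to 1.2 points with mpMRI, depending on whether the relative hazard of 0.55 extends to death. It becomes material later, reaching 5.1 to 7.8 points with TURBT at 4.5 years. These sizes assume constant hazards and a division of the 0.23 per year that the documents do not give.

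It would go too far to say that the arm difference is bound to be exaggerated in favour of mpMRI. It is exaggerated in cases (a) and (b), but the discrepancy nearly disappears if deaths without progression are more frequent with mpMRI. That dependence is a reason to report both causes.

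**What to change.** In the Statistical methods section, separate TTP from PFS:

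- Keep Kaplan-Meier curves for PFS.
- Present TTP as Aalen-Johansen cumulative incidence by arm, with death without progression as the competing event.
- Keep the log-rank test and the proportional hazards model for TTP, and state that they are cause-specific with deaths censored.
- Report the cause-specific hazard ratio for death without progression alongside the one for progression. Gray's test is optional.

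The analysis plan should use the same wording. The cost is a sentence or two of text. Dates of progression and death are already needed for PFS, so no new data are required, standard software suffices, and neither the design nor the sample size changes. Analysis is scheduled for months 67 to 72, so the change can be made well before then.

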##### Quality of life

To assess generic health-related quality of life, the EuroQol 5 Dimension 5 Level (EQ-5D-5L) questionnaire^17^ will be administered to all participating patients on paper at baseline (inclusion in study), 6 months, 12 months and 24 months post-randomisation.

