##### Cost-effectiveness

Cost-effectiveness will be analysed from a healthcare perspective, using a 2-year time horizon. Effectiveness will be measured in terms of quality-adjusted life years (QALYs), following the Dutch guideline for economic evaluation.^19^ QALYs will be based on the patient-reported EQ-5D-5L scores. From these scores, utility values will be calculated using the Dutch tariff.^20^ Based on these utility values, QALYs will be computed per patient using the area under the curve approach. Costs and QALYs in the second year of follow-up will be discounted at a rate of 3% and 1.5%, respectively, based on the Dutch guideline for economic evaluation. Absolute means and mean differences between the arms in terms of costs and QALYs will be calculated. As cost data are generally highly skewed, bootstrapping will be performed to estimate 95% CIs around the costs and effects.^21^ If the new strategy is both more costly and more effective, incremental cost-effectiveness ratios (ICERs) will be calculated by dividing the estimated differences in costs by the difference in QALYs. This will result in incremental costs per QALY gained. If the new strategy is less costly and more effective, it is considered to dominate the standard strategy. If it is less costly and less effective, ICERs will be calculated to derive the additional savings per QALY lost. If the new strategy is more costly and less effective, it is considered to be dominated by the current strategy. Cost-effectiveness acceptability curves will be derived, illustrating the probability of cost-effectiveness against different cost-effectiveness thresholds.^22^ All analyses will be performed on an intention-to-treat basis. The impact of missing data will be assessed with single imputation nested in the bootstrap percentile method.^23^

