### Data collection methods

Data will be collected using standardised procedures to ensure consistency and accuracy across all participating centres. Clinical and imaging data, including mpMRI results and biopsy findings, will be recorded in the electronic data capture system CASTOR. Quality of life questionnaires (EQ-5D-5L) will be administered on paper, collected via mail and entered into CASTOR by trained study personnel. All data collection forms and procedures will be pilot-tested prior to study initiation to minimise missing data and measurement errors. Data collectors and outcome assessors will be trained and monitored regularly to maintain data quality.

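### The missing-data check named in the protocol, imputed against complete case, cannot show whether unreturned EQ-5D-5L forms hide worse health than the observed data predict

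*Protocol article*

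**What the plan says.** Two sections of the protocol article deal with missing data.

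- Statistical methods, after the paragraphs on PFS and time to definitive treatment: "Missing data will be handled using multiple imputation with sensitivity analyses comparing imputed and complete case results". No endpoint or imputation model is named. The next sentence leaves room for more: "Prespecified subgroup and sensitivity analyses, for instance, stratified by use of neoadjuvant chemotherapy, will be conducted".
- Cost-effectiveness, for costs and QALYs: "The impact of missing data will be assessed with single imputation nested in the bootstrap percentile method".

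The data at risk are the quality-of-life forms. They are given "on paper at baseline (inclusion in study), 6 months, 12 months and 24 months post-randomisation" and, under Data collection methods, handled as follows: "Quality of life questionnaires (EQ-5D-5L) will be administered on paper, collected via mail and entered into CASTOR by trained study personnel". Under Cost-effectiveness, "QALYs will be computed per patient using the area under the curve approach", using utilities from these forms, with second-year QALYs discounted at 1.5%. Quality of life and cost-effectiveness are both secondary outcomes.

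**The concern.** A sensitivity analysis should vary the assumption that is in doubt. For mailed forms, the doubt is whether patients who do not reply are in worse health than their recorded data suggest. Multiple imputation as usually run assumes they are not, given what is recorded. Complete-case analysis does not relax that assumption; it replaces it with another that is equally untestable and generally stronger. Single imputation inside a bootstrap changes how uncertainty is carried, not what is assumed about non-responders.

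Agreement between the imputed and complete-case results could therefore be read as robustness when the relevant question has not been asked. The mechanism is plausible here: patients face cystectomy, chemotherapy or chemoradiotherapy, and health can decline in the 6 to 12 months between forms. At stake are the reported utilities, the QALY difference and the incremental cost-effectiveness ratio.

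**Working it through.** **The plan's own figures.** The article gives no expected rate of missing forms, so there is no missing-data figure to reproduce. The design figures used below do reproduce:

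- Events = 4(1.96 + 0.84)²/(ln 0.55)² ≈ 88.
- With 0.23 events and 0.1 censorings per year over 3.25 years, event probabilities are 0.4585 (TURBT) and 0.2910 (mpMRI), mean 0.3747.
- 88/0.3747/2 = 117.4 per arm, and 117/0.65 = 180.

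**Step 1: weight of the follow-up forms.** Trapezoids on 0, 6, 12 and 24 months, with year 2 divided by 1.015:

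- 6 months: 0.25 + 0.25 = 0.50
- 12 months: 0.25 + 0.50/1.015 = 0.743
- 24 months: 0.50/1.015 = 0.493
- Sum: 1.735 (1.75 undiscounted)

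**Step 2: bias formula.** Let m be the share of forms missing and d the amount by which true utility lies below the imputed value. Mean QALYs in an arm are overstated by m × d × 1.735. The between-arm difference is biased by the difference of these two products, which is zero if m and d are the same in both arms.

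Bias in the QALY difference, same d in both arms (m and d are assumptions):

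| Arm difference in m | d = 0.10 | d = 0.20 |
|---|---|---|
| 3 points | 0.005 | 0.010 |
| 5 points | 0.009 | 0.017 |
| 10 points | 0.017 | 0.035 |

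**Step 3: how large an arm difference in m is credible.** At 0.23 per year and a hazard ratio of 0.55, cumulative PFS events differ between arms by:

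- 6 months: exp(−0.0633) − exp(−0.115) = 4.7 points
- 12 months: exp(−0.1265) − exp(−0.23) = 8.7 points
- 24 months: exp(−0.253) − exp(−0.46) = 14.5 points

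Weighted: (0.50 × 4.7 + 0.743 × 8.7 + 0.493 × 14.5)/1.735 = 9.2 points. If PFS events alone drove the imbalance, 10 points would need more than every patient with an event failing to reply while everyone else replied. With an assumed excess non-return of 30 to 50 points after an event, the difference is 2.8 to 4.6 points. With d of 0.10 to 0.15 the bias is then 0.028 × 0.10 × 1.735 = 0.005 to 0.046 × 0.15 × 1.735 = 0.012 QALY.

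**Step 4: does the named check give a warning?** Large-sample simulation, all values assumed: progression at 0.8 × 0.23 per year with hazard ratio 0.55; baseline utility 0.80 (SD 0.12); a fall of 0.20 after progression and of 0.08 per SD of unrecorded illness. Non-return is logistic, with intercept −1.8 and log-odds 1.5 for progression and 1.0 per SD of unrecorded illness where each applies. Imputation includes progression. Deaths are not modelled.

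| Cause of non-return | True difference | Complete case | Imputed |
|---|---|---|---|
| (a) Recorded progression | 0.026 | 0.013 | 0.026 |
| (b) Unrecorded illness, same in both arms | 0.026 | 0.026 | 0.026 |
| (c) Both (a) and (b) | 0.027 | 0.015 | 0.025 |
| (d) As (b), but TURBT intercept −1.3 (25% v 18% missing) | 0.028 | 0.021 | 0.020 |

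A further set of assumed values, with unrecorded illness differing by arm, gave 0.034 (truth), 0.022 (complete case) and 0.022 (imputed).

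In (b) the arm means are wrong although the two analyses agree: TURBT 1.548 for both against a true 1.526, and mpMRI 1.574 for both against 1.552. In (d) the two analyses agree closely and both miss the true difference. In (a) and (c) they disagree, so the check does signal.

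**The case against.** The strongest objection is that this is detail for the statistical analysis plan, which the article says exists and which is not shown. The article does not claim that the comparison tests the missing-at-random assumption, and it leaves its list of sensitivity analyses open. This stands in part. The absence of a missing-not-at-random analysis from a journal article is not itself an error. What can be criticised is the check that the article chose to name, because it leaves the main doubt about mailed forms unexamined.

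A reader might also infer stronger statements that the document does not support:

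- *That this is the only check planned.* The Statistical methods section announces further analyses, and Cost-effectiveness sets its own method for QALYs. It is the only one named for missing data under Statistical methods.
- *That neither analysis can allow for ill patients.* Progression is the main component of the primary outcome and is sought on imaging every 6 months. Imputation that uses it corrects that part, as rows (a) and (c) show.
- *That the two analyses will agree and the QALY difference will be biased.* This needs non-return tied to unrecorded illness and an arm difference in m or d. With equal mechanisms only the arm means are biased.
- *That the bias is a large share of the expected QALY gain.* The design rates give 0.164 more progression-free years over 2 years (1.767 − 1.603), but turning this into QALYs needs utilities and a life-year gain that the article does not give. PFS events also include deaths, which conventionally count as utility zero and not as a missing form.

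**Conclusion.** The point holds in limited form. Comparing imputed with complete-case results cannot probe whether unreturned EQ-5D-5L forms hide worse health than the recorded data predict, and the single imputation planned for QALYs ordinarily shares the same assumption. Where non-return reflects unrecorded illness and differs by arm, the two results can agree and both be wrong for the QALY difference.

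The size cannot be fixed from the document. Under the assumptions shown it is roughly 0.005 to 0.035 QALY. Values near 0.035 need a 10-point imbalance at every follow-up form and a deficit of 0.20 below the imputed value, which is extreme. This is a minor, worthwhile improvement to secondary outcomes. The primary PFS analysis and the sample size are not affected.

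**What to change.** For EQ-5D-5L and QALYs, in Statistical methods and Cost-effectiveness:

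1. Include recorded progression status and date in the imputation model.
2. Add a delta-adjusted imputation that lowers imputed utilities by 0.05, 0.10, 0.15 and 0.20, in both arms jointly and in each arm separately.
3. Report the shift at which the QALY conclusion changes.
4. Keep the complete-case result as description only.

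This uses data already collected. The cost is a little more analysis and a wider reported range of QALY results.
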